### Participants/eligibility criteria

We will study women who developed postmenstrual spotting after a CS, and in whom sonohysterography has shown a niche of at least 2 mm depth and a residual myometrium of at least 3 mm. Postmenstrual spotting is defined as two or more days of intermenstrual spotting or as two or more days of brownish discharge immediately after the menstrual period in case the total period of the menstrual bleeding exceeds 7 days, if the period is shorter then 7 days the brownish discharge is considered to be normal.

In these women, saline or gel sonohysterography (SIS or GIS) will be performed as part of routine diagnostic work-up for identification of the origin of the bleeding. Exclusion criteria are a residual myometrium less than 3 mm at sonohysterography, age below 18 years, pregnancy, a (suspected) malignancy, contra-indications for spinal of general anaesthesia, uterine or cervical polyps, submucosal fibroids, atypical endometrial cells, cervical dysplasia, cervical or pelvic infection, hydrosalpinx that communicates with the uterus or an irregular cycle (>35 days or intercycle variation of 2 weeks or more).

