#### Sample size

Based on a systematic review of the literature executed in 2011 we identified one relevant manuscript reporting on a reduction in postmenstrual abnormal uterine bloodloss (PAUB) with an estimated median reduction of 3.8 days after a hysteroscopic niche resection compared to baseline [27]. At baseline, included patients had mean spotting of 7.5 days with a standard deviation of 2.7. Estimated postmenstrual spotting reduced from 7.5 to 3.7 days (see box and whisker plots). Given the fact that the ranges at baseline and after therapy were more or less similar we estimated the SD to be approximately 2.7. However given the lack of a control group without treatment it cannot be excluded that regression to the mean have played a role and may have induced an overestimation of the effect. Given these uncertainties we decided to base our sample size on the difference in postmenstrual spotting days that were considered to be clinically relevant and this should be lower than the previously reported difference of 3.8 in order to prevent insufficient power. Based on experience and confirmed in a survey among patients (unpublished), we considered 2 days to be clinically relevant and a dropout rate of 20 % to be realistic and used these parameters to calculate a sample size to achieve a power of 90 %.

In summary, assuming a difference of postmenstrual spotting of 2 days to be clinical relevant with an estimated SD of 2.7, a dropout rate of 20 %, we need to include 50 patients in each arm to achieve a power of 90 %.

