#### Statistical analysis

Analyses will be performed according to intention-to-treat principle and additionally by per protocol analysis. All tests will be performed two sided and a *p*-value <0.05 will be considered as statistically significant. The difference between the two groups at 6 months follow-up regarding total number of postmenstrual spotting days during one menstrual cycle, duration of menstrual bleeding, number of days of brownish discharge, menstrual pain, experienced discomfort of spotting and of menstrual pain, SF-36 domain scores and EuroQol will be analysed using linear regression analyses, adjusted for relevant baseline values. Potentially relevant confounders are additional hormonal therapy, smoking and use of anticoagulation. Logistic regression analysis will be used to evaluate the existence of (midcycle) intra-uterine fluid. To compare satisfaction with treatment, reported on a 0–5 point scale at six months a (multinominal) logistic regression analysis will be used.

We have planned four subgroup analyses, for:

1) Total days of spotting at the end of the menstruation and intermenstrual spotting >25^th^ centile versus ≤ 25^th^ centile and >75^th^ centile or ≤75^th^ centile at baseline;

2) Number of days postmenstrual spotting >25^th^ centile versus ≤2 25^th^ centile and >75^th^ centile versus ≤75^th^ centile at baseline;

3) Small versus larger niches (using a cut-off of residual myometrium of 3 and 5 mm and <50 % of total myometrial thickness (sum of RM and niche depth) at baseline;

4) A history of 1 versus more than 1 CS at baseline.

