### Potential impact and implications

This trial will provide evidence for patients, healthcare providers and policy makers on the (cost) effectiveness of hysteroscopic resection of a niche versus expectant management in women with postmenstrual spotting and a niche with sufficient residual myometrium to perform a hysteroscopic niche resection. It is important to realize that not all niches cause symptoms, and as the treatment is predominantly performed to relieve symptoms, niches without symptoms should not be treated by a hysteroscopic niche resection. In addition it is important to realize that we only include patients with relatively small niches thus the outcomes can’t be extrapolated to patients with large niches. In patients with large niches, i.e. thin residual myometrium of less then 3 mm a hysteroscopic niche resection is expected to be at higher risk of bladder injury and uterine perforations.

Based on results of this study, implementation of the hysteroscopic niche resection in daily practice can be discussed and long-term complications of a CS can possibly be reduced. The patient reported outcomes could inform future patients about the expected outcomes of both niche resection and expectant management and support shared decision making.

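### Read literally, the niche-size subgroup's 3 mm cut-off splits at the trial's own entry floor, and cutting baseline spotting days at quartiles gives up nearly half the information on effect modification

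*Protocol article*

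**What the plan says.** All references are to the protocol article.

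- **Niche-size subgroup** (Statistical analysis, third planned subgroup): "Small versus larger niches (using a cut-off of residual myometrium of 3 and 5 mm", together with a criterion of less than 50 % of total myometrial thickness, where total thickness is residual myometrium plus niche depth.
- **Eligibility** (Participants/eligibility criteria): a residual myometrium of at least 3 mm is required, and the converse is an exclusion: "Exclusion criteria are a residual myometrium less than 3 mm at sonohysterography". The Abstract and the section on procedures, recruitment and randomisation repeat the 3 mm floor.
- **Scope of inference** (Potential impact and implications): only relatively small niches are included, and results cannot be carried over to large ones. The risk statement there begins "In patients with large niches, i.e. thin residual myometrium of less then 3 mm", which equates a large niche with a value below the entry floor.
- **Spotting subgroups** (Statistical analysis, first and second planned subgroups): the first modifier is "Total days of spotting at the end of the menstruation and intermenstrual spotting" and the second is the number of postmenstrual spotting days. Each is cut at both the 25th and the 75th centile of its baseline distribution.
- **Power** (Sample size): the 90 % applies to the overall comparison. No power is claimed for any subgroup.

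**The concern.** A cut-off is useful only if women fall on both sides of it. The 3 mm value is the limit below which women are not enrolled, so as a dividing line within the trial population it separates almost nothing. An analyst following the text could not tell which comparison was intended, and the choice would then be made with the data in view.

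The spotting subgroups raise a different problem. The article fixes the form of the modifier by cutting a count of days at its quartiles. In a trial of 100 women this makes the smaller group very small and treats all women on one side of the cut as alike. Whether benefit depends on niche size or symptom load matters to patients and surgeons, and this coding uses the available data poorly.

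**Working it through.** **1. The 3 mm cut-off against eligibility**

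| Reading of the 3 mm value | Consequence in the enrolled population |
|---|---|
| Below 3 versus 3 or more | Lower group has expected count 0 |
| 3 or less versus above 3 | Lower group is only women measuring exactly 3 mm |
| Lower bound of a 3–5 mm band, versus above 5 mm | Both groups can be populated; 3 mm is the entry floor and does no dividing |

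The 5 mm cut and the below-50 % criterion are not affected. The distribution of residual myometrium is not given, so the sizes of the 3–5 mm and above-5 mm groups cannot be computed.

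**2. Inputs for the quartile check**

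- Target difference 2 days: "assuming a difference of postmenstrual spotting of 2 days to be clinical relevant" (Sample size).
- SD 2.7 days, dropout 20 %, 50 per arm (Sample size).
- "All tests will be performed two sided", at the 5 % level (Statistical analysis).
- Overall power: "used these parameters to calculate a sample size to achieve a power of 90" % (Sample size).

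**3. The plan's own figure**

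n per arm = 2 × (1.960 + 1.282)² × 2.7² / 2² = 38.3, so 39. Allowing for dropout, 39 / 0.80 = 48.75, so 49. The t-test version gives 39.3, or 49.1 after dropout. The stated 50 per arm is reproduced to within rounding.

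**4. Precision in an outer quartile**

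Evaluable women: 100 × 0.80 = 80. A quarter is 20, or 10 per arm; the remainder is 60, or 30 per arm.

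- SE in the quartile = 2.7 × √(2/10) = 1.21 days.
- 95 % CI half-width with t on 18 df = 2.10 × 1.21 = 2.5 days (2.4 by the normal approximation).
- Power for 2 days = 35 % (t-test) or 38 % (normal approximation).
- Power for 2 days in the larger group of 30 per arm = 82 %.

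**5. Quartile-versus-rest interaction**

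- SE = 2.7 × √(2/10 + 2/30) = 1.39 days.
- Detectable difference at 80 % power = (1.960 + 0.842) × 1.39 = 3.9 days. This is about twice the 2-day target and about as large as the whole 3.8-day before-after reduction cited in the Sample size section.
- Power for a 2-day interaction = 30 %.
- With all 100 women evaluable (12.5 per arm in the quartile), the detectable difference is 3.5 days.
- A median split of 80 women would detect 3.4 days.

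**6. What the quartile coding costs**

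For a normal modifier, the information kept by a 25/75 split relative to a linear term is φ(0.674)² / (0.25 × 0.75) = 0.318² / 0.1875 = 0.54.

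As a cross-check, the linear interaction slope has SE = 2 × 2.7 / √80 = 0.60 days per SD, so it detects 2.80 × 0.60 = 1.7 days per SD. The means of an outer quartile and of the rest lie 0.318/0.25 + 0.318/0.75 = 1.70 SD apart, so 3.9 days corresponds to 3.9 / 1.70 = 2.3 days per SD. Then (1.7 / 2.3)² is about 0.54, which agrees.

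**7. Could baseline adjustment remove the problem?**

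Adjustment scales the SE by √(1 − r²), where r is the correlation of baseline with outcome. To bring 3.9 down to 2 days, r² would have to be 1 − (2/3.906)² = 0.74, or r about 0.86. The article gives no value of r.

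**The case against.** A reader might infer that one planned subgroup is empty by design and cannot be analysed. The article does not support that in absolute form. The phrase naming 3 and 5 mm can be taken as the bounds of a band, which gives 3–5 mm versus more than 5 mm with both groups populated. The procedures section also measures niches by plain and contrast sonography in two planes, and its wording about one of the planes could be read to admit a lower value in the other plane. That section's own safety rationale and the eligibility criteria point the other way. At most one of three niche criteria is affected. What remains is that on the band reading 3 mm is not a cut-off, so the wording still needs correcting.

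On the quartiles, it is fair to say that trial size accounts for much of the imprecision: a median split improves the detectable interaction only from 3.9 to 3.4 days, and the larger group has 82 % power for 2 days. Spotting is a whole-day count with an entry minimum of two days, so ties can move the groups away from 25 % and the normal-modifier efficiency is approximate. The planned baseline adjustment would narrow the intervals. All of this stands. It does not rescue the coding, because the alternative is a continuous term and not a median split, and the comparison per SD (1.7 against 2.3 days) holds at the same trial size.

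It can also be said that interaction tests and multiplicity are usually left to an analysis plan. That is right, and their absence here is not part of this point. The article does, however, fix the centile cuts itself.

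**Conclusion.** The point holds in two limited parts. First, the 3 mm cut-off conflicts with the 3 mm entry floor unless it is read as the lower edge of a 3–5 mm band, and the sections need to be reconciled. Second, cutting baseline spotting days at quartiles is an inefficient choice. With 80 evaluable women, about 10 per arm fall in an outer quartile, giving 35 % power for 2 days, a half-width of about 2.5 days and a detectable interaction of about 3.9 days, and about 54 % of the information in a continuous modifier is kept.

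These figures assume an exact 25/75 split, equal arms within groups, an SD of 2.7 in every group, a roughly normal modifier and no gain from baseline adjustment.

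Three stronger inferences are not supported:

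- That weak subgroups contradict the power claim. The 90 % was stated only for the overall comparison.
- That a family-wise false-positive rate can be computed by counting the listed splits as independent tests. Cuts of the same or related variables are correlated, and on the literal reading one of them cannot be run.
- That having two similar spotting measures is an error. Keeping one would be tidier, but that is a preference.

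The primary result is untouched.

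**What to change.** 1. Remove 3 mm as a subgroup cut-off, or state the groups as 3–5 mm versus more than 5 mm. Name the measurement (modality and plane) that defines them, and say how they relate to the below-50 % criterion. Reconcile the Statistical analysis section with the eligibility criteria, the procedures section and the statement on impact. This concerns only the description of the subgroup; it implies no view on where the eligibility limit should lie.
2. Test effect modification by adding a treatment-by-covariate interaction to the linear regression already planned, one modifier at a time: residual myometrium in mm, residual myometrium as a share of total thickness, and baseline spotting days, each as a continuous term. The history of one versus more than one caesarean section stays binary.
3. Show the 5 mm and centile groups descriptively, with estimates and intervals.

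The cost is wording only, with no new data. The downside is that a linear interaction assumes a monotone trend; a plot of the treatment difference against the modifier can check this. Precision will still be limited by a trial of 100 women, and the report should say so.

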### Economic evaluation

The economic evaluation will be performed alongside the randomised controlled trial. Both a cost-effectiveness analysis as a cost-utility analysis will be performed from the societal perspective. In the cost-effectiveness analysis, the reduction in postmenstrual spotting days will be used as the primary outcome. In the cost-utility analysis, societal costs will be related to QALYs over 6 months. Costs that will be included are direct healthcare costs (costs of the hysteroscopic niche resection, use of healthcare services such as outpatient visits, hospital admissions, laboratory and imaging tests, visits to health care providers outside the hospital, medication, etcetera), direct non-healthcare costs (i.e. informal care), and indirect non-healthcare costs (absenteeism and presenteeism from paid and unpaid work).

We hypothesize that hysteroscopic niche resection will reduce postmenstrual spotting and related medical consultations, applied therapies and sick leave and as a consequence will be cost-effective in comparison with the expectant management strategy.

Analyses will be performed according to the intention-to-treat principle. Missing cost and effect data will be imputed using multiple imputation [34]. The imputation will include variables that are related to missing data or the outcome measure, and variables that differ at baseline between the groups. To account for the skewed distribution of costs predictive mean matching will be used in the multiple imputation. The number of imputed data sets to be created will be determined based on the fraction of missing information [35]. All datasets will be analyzed separately and the results of the 20 analyses will be pooled using Rubin’s rules [36]. Incremental cost effectiveness ratios (ICERs) will be calculated by dividing the differences in mean total costs between both treatment groups, by the difference in mean effects between both treatment groups [36]. To avoid double counting, productivity costs due to sick leave will be excluded in the ICER with sick leave as effect measure. The incremental cost utility ratio will be calculated by dividing the incremental costs by the difference in QALYs between both treatment groups. To account for the typically skewed distribution of costs, bias-corrected and accelerated bootstrapping (5000 replications) will be used to estimate the 95 % confidence intervals around the mean cost differences and the uncertainty surrounding the ICERs. The bootstrapped ICERs will be graphically presented in cost-effectiveness planes [37]. Cost-effectiveness acceptability curves will be estimated to show the probability of the intervention program to be cost-effective in comparison with usual care for a range of different ceiling ratios, thereby showing decision uncertainty [38].

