At the time of randomisation, baseline, obstetric and medical history are reported in the case report file. The patient will receive digital online secured questionnaires at baseline, 3 and 6 months after randomisation about their menstrual pattern and uterine bleeding, will complete a validated menstrual bleeding score chart [28], validated questions to report on quality of life (SF-36: Short Form 36 [29, 30] and Euro-QOL 5D: Euro Quality of Life in 5 dimensions [31]), sexual function (FSFI: Female Sexual Function Index) [32] and absence from work (HLQ: Health and Labour [33]). Medical consultation, medication use and received additional therapies will be registered at the same timepoints in an online diary. Any received additional therapy will be registered in the case report file.

Three months after randomisation all patients will undergo transvaginal sonography to register all niche features as at baseline. Patients will be motivated to undergo a SIS or GIS, however saline or gel instillation will be omitted in case patients experienced too much discomfort during this procedure at baseline (see Fig. 4 for the flowchart).

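### The cost-utility ratio is defined on a simple difference in QALYs with no baseline adjustment named, although baseline EQ-5D is collected and adjusting for it would gain precision at almost no cost

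*Protocol article*

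**What the plan says.** The Economic evaluation section of the protocol article defines both ratios from group differences. For cost-effectiveness: "Incremental cost effectiveness ratios (ICERs) will be calculated by dividing the differences in mean total costs between both treatment groups", and the divisor is described as "by the difference in mean effects between both treatment groups". For cost-utility: "The incremental cost utility ratio will be calculated by dividing the incremental costs by the difference in QALYs between both treatment groups". The horizon is given by "societal costs will be related to QALYs over 6 months". The effect in the cost-effectiveness analysis is described as follows: "the reduction in postmenstrual spotting days will be used as the primary outcome".

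Baseline variables appear in the economic methods once, as predictors for missing data: "The imputation will include variables that are related to missing data or the outcome measure, and variables that differ at baseline between the groups".

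The Statistical analysis section treats related measurements differently. It compares the groups at 6 months, and "SF-36 domain scores and EuroQol will be analysed using linear regression analyses, adjusted for relevant baseline values"; spotting days are in the same list of outcomes.

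The section on procedures and collection of baseline data states: "The patient will receive digital online secured questionnaires at baseline, 3 and 6 months after randomisation". EQ-5D is among these instruments, so baseline utility will be available. Randomisation is stratified by centre alone, and the Sample size section gives 50 patients per arm.

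**The concern.** With EQ-5D at three times, the usual way to obtain a 6-month QALY is the area under the utility curve. Baseline utility is then a component of the QALY, although treatment cannot have affected it. It is normally also correlated with utility at 3 and 6 months. A chance difference in baseline utility therefore passes into a simple QALY difference by both routes. Randomisation stratified by centre alone does not prevent this, and 50 per arm is few enough for it to matter.

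Using baseline variables as imputation predictors does not solve the problem. It improves the imputed values but does not adjust the comparison between arms.

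At stake are the precision of the incremental QALY estimate and how well it reflects the patients actually randomised. The cost-utility ratio, the cost-effectiveness plane and the acceptability curve are all built on it. There is a smaller, related problem for spotting. The economic section does not say whether the reduction is a change from baseline or a difference between groups, nor whether it is the adjusted estimate from the clinical analysis.

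**Working it through.** **Sample size, reproduced first.** Inputs from the Sample size and Statistical analysis sections: difference 2 days, SD 2.7, power 90%, two-sided 0.05, dropout 20%.

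- Normal approximation: 2 × [2.7 × (1.960 + 1.282) / 2]² = 38.3, so 39 per arm; 39 / 0.8 = 48.75, so 49.
- Exact t-test: 40 evaluable per arm gives 90.5% power; 40 / 0.8 = 50.

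The stated 50 per arm is reproduced, and nothing below changes it.

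**Assumptions for the QALY illustration.** From the document: EQ-5D at 0, 3 and 6 months, a 6-month horizon and 50 per arm. Assumed, because the document does not give them: the trapezoid rule, the utility SD (equal at all times) and the correlations.

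**Step 1. Weights.** Over 0.5 years the trapezoid weights are 0.125 (baseline), 0.25 (month 3) and 0.125 (month 6). Baseline carries 0.125 / 0.5 = 25% of the total weight.

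**Step 2. Slope of QALY on baseline utility.** b = 0.125 + (0.25 + 0.125) × r, where r is the correlation of baseline with follow-up. At r = 0.5, b = 0.3125.

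**Step 3. Chance imbalance.** SE of the baseline difference = SD × √(2/50). At SD 0.20 this is 0.04. Carried into the QALY difference: 0.3125 × 0.04 = 0.0125, so the 95% chance shift is 1.96 × 0.0125 = ±0.0245.

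**Step 4. Precision with and without adjustment** (SD 0.20, r = 0.5, month-3/month-6 correlation 0.6).

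- Sum of squared weights: 0.015625 + 0.0625 + 0.015625 = 0.09375.
- Cross terms: 2 × (0.5 × 0.125 × 0.25 + 0.5 × 0.125 × 0.125 + 0.6 × 0.25 × 0.125) = 0.084375.
- QALY variance: 0.04 × 0.178125 = 0.007125; SD 0.0844.
- Part explained by baseline: (0.3125 × 0.20)² = 0.003906, which is 55% of the variance.
- Residual SD: √(0.007125 − 0.003906) = 0.0567.
- SE of the difference: 0.0844 × 0.2 = 0.0169 unadjusted; 0.0567 × 0.2 = 0.0113 adjusted, about one third smaller.

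With one common correlation of 0.5 at all times, the two standard errors are 0.0166 and 0.0109.

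**Step 5. Range (50 per arm, common correlation).**

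| SD | r | SE of baseline difference | SE carried into QALY difference | 95% chance shift (±) |
|---|---|---|---|---|
| 0.10 | 0.3 | 0.020 | 0.0048 | 0.009 |
| 0.20 | 0.5 | 0.040 | 0.0125 | 0.025 |
| 0.25 | 0.7 | 0.050 | 0.0194 | 0.038 |

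**Step 6. Spotting.** With the plan's SD of 2.7 at both times, the SE of the chance baseline difference is 2.7 × √(2/50) = 0.54 days. A comparison of follow-up values alone carries r × 0.54. A change score carries (1 − r) × 0.54 with the opposite sign. For r from 0.3 to 0.7, each runs between 0.16 and 0.38 days, against a target difference of 2 days. The two readings of the undefined reduction thus respond to baseline imbalance in opposite directions. The baseline-adjusted estimate avoids both.

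**The case against.** The strongest reply is that the article never says the differences are unadjusted. The wording is the generic definition of the ratio, and a regression-adjusted mean difference also satisfies it. A condensed article may leave covariates to a fuller protocol or a health economic plan that is not shown. This stands in part: the document does not establish that the analysis will in fact be unadjusted. However, the section goes into detail on imputation, pooling, bootstrapping and acceptability curves, and it mentions baseline differences only for the imputation. As written, the estimator is a simple difference, and there is a better one that uses data already collected.

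Four stronger readings are tempting, and the document does not support them.

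- *The cost-utility result is biased.* Chance imbalance under randomisation is not systematic bias. The shift of ±0.0245 lies within the unadjusted sampling error (1.96 × 0.0169 = ±0.033) that the planned bootstrap already carries. It is not an additional, undeclared error.
- *Baseline spotting enters the QALY directly.* Spotting days are not a component of a QALY, so any link is indirect. If the reduction is a change from baseline, baseline spotting has already been subtracted, although a change score over-corrects compared with regression.
- *The trial will report two conflicting effects for the same endpoint.* EuroQol at 6 months and QALYs accumulated over 6 months are different quantities. For spotting, the conflict depends on how an undefined term is read.
- *Imbalance will reverse the sign of the ratio.* That depends on the true QALY gain, for which the document gives no figure.

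It is also fair to say that every utility input above is assumed. At the low end of the range the shift is under 0.01 QALY.

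**Conclusion.** The point holds as a concrete improvement to a secondary analysis. As published, the incremental QALY is a simple difference with no baseline adjustment named, while the same article adjusts EuroQol for baseline in the clinical analysis and collects the covariate needed.

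The consequence is avoidable imprecision and exposure to chance imbalance in this one trial. Under the main illustration, adjustment lowers the standard error of the QALY difference from about 0.017 to 0.011. Over the assumed ranges, the 95% chance shift due to baseline is about 0.009 to 0.038 QALY. These figures rest on trapezoidal QALYs and on assumed SDs and correlations. They show the order of magnitude and do not predict this trial's result.

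For spotting, the defect is mainly an undefined effect measure. The primary outcome and the sample size are not affected.

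**What to change.** State in the Economic evaluation section that:

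1. Incremental QALYs are estimated by regression on treatment and baseline EQ-5D utility, refitted within each imputed and bootstrapped data set.
2. That adjusted estimate is the one used in the cost-utility ratio, the cost-effectiveness plane and the acceptability curve.
3. The effect in the cost-effectiveness analysis is the baseline-adjusted difference in spotting days defined in the Statistical analysis section. This also settles what is meant by reduction.

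If a fuller plan already specifies this, a sentence pointing to it is enough. Joint modelling of costs and effects by seemingly unrelated regression, or adding centre as a covariate, would be acceptable, but this is a preference and not needed to resolve the point.

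The cost is a few sentences and a few lines of analysis code. No new data, visits or patients are needed, because baseline EQ-5D is already collected.
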